### 2.9. Economic Evaluation

The present study examines the cost-effectiveness of the telephone counseling in accordance with the CHEERS checklist [48]. Four types of costs will be considered: (1) the costs of offering the interventions; (2) recruitment costs for each implementation approach and channel; (3) costs stemming from health care uptake; and (4) costs stemming from losses in productivity, in both paid work and volunteer jobs. Costs of the interventions and implementation channels and approaches (e.g., sending materials to health care professionals and advertisements on Facebook) will be monitored during the study. Other costs will be calculated by using standard cost prices (for reference year 2014), which are published in the Dutch guideline for costing [49]. The data on costs stemming from health care uptake and losses in productivity will be collected using the Trimbos/iMTA Questionnaire on Costs associated with Psychiatric illness (TiC-P) [50]. The TiC-P is the most widely used patient-reported measure of health service utilization in The Netherlands [51]. The cost-effectiveness analyses (CEA) will be conducted along the RCT, with 7-day point prevalence abstinence at three months post-intervention as the primary outcome (i.e., the incremental effect). The incremental costs will be calculated as the average cost difference between the conditions. Both the incremental effect and incremental costs will be combined to compute the incremental cost-effectiveness ratio (ICER; incremental costs/incremental effects). To manage stochastic uncertainty, 2500 non-parametric bootstraps will be used and the bootstrapped ICERs will be plotted on the ICER plane. Based on the four quadrants of the ICER plane, four scenarios are possible regarding the telephone counseling, which can: (1) costs more and be more effective; (2) costs more and be less effective; (3) costs less and be less effective; and (4) costs less and be more effective. As seen from a health-economics perspective, the second and fourth scenarios are clear cut cases for decision-makers, with the second scenario being the least attractive (and the intervention is dominated by its alternative (the self-help brochure)) and the fourth scenario being the most attractive, and decision-makers will opt for the intervention. On the other hand, the first scenario is more difficult for decision-makers. In this scenario, one needs to decide how much one is willing to pay for an additional unit of effect (one extra parent who was successful in refraining to smoke) [52]. To facilitate this decision, an ICER acceptability curve will be plotted with the probability that one deems the intervention to be cost-effective (on the *y*-axis) against various willingness-to-pay ceilings (on the *x*-axis). Finally, the CEA will be completed by performing one-way sensitivity analyses directed at uncertainties in major cost-drivers. This is done to ascertain the robustness of the CEA findings.

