### 2.5. Data Collection

The timing of the data collection will be different for each implementation channel. Parents will be recruited gradually from September 2016 to September 2018. This means that the data of the two assessments will be obtained at different moments during the data collection (i.e., at the start of the study and at 3 months after the start of the intervention). All parents will receive a personal invitation by e-mail to complete two questionnaires online at a secured website. The web survey software application Jambo (January 2017) will be used to collect parents’ answers. At the end of the study, multiple family excursions will be raffled among parents (e.g., free entry permits for an amusement park). The parents will be told that the raffles will not be part of the parents’ incentives to enroll in the study, but to complete the two online questionnaires.

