### 2.6. Randomization

An independent member of the research group will conduct randomization using a computer-generated allocation sequence. Parents will be stratified by educational level (i.e., low: no high school diploma/no vocational training; medium: vocational training or high school diploma; high: college degree), implementation channel (i.e., primary schools, health care, youth health care, and online mass media), and number of cigarettes smoked per day (i.e., less than 10; 10–20; 21 or more). When both parents live in the same household and participate in this study, randomization will be carried out at household level to avoid contamination between the two conditions.

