
### 2.10. Statistical Analyses

Statistical analyses will be carried out to assess whether the randomization results in an equal baseline distribution of relevant participant characteristics across conditions. In case of group differences at baseline, confounding variables will be included in subsequent analyses. All analyses will be conducted in accordance with the intention-to-treat principle (i.e., all parents randomized to one of the two conditions will be included in the analyses examining the study hypotheses) as per the Consolidated Standards of Reporting Trials [53]. Moreover, a completers-only analyses will be conducted, i.e., only parents with outcome data on all assessments will be included in the analyses. To compare cessation rates across different groups, logistic regression analyses will be conducted. In addition, Mplus will be used to test for moderation and subsequently, multi-group testing with bootstrapping will be conducted to assess differences between recruitment approaches. Effect sizes and 95% confidence intervals (CI) will be reported to determine the magnitude and effect of the intervention.

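### The economic evaluation names no adjustment for baseline costs, and the conditional adjustment rule does not say whether it covers costs; this gives up precision in a trial of about 79 parents per arm

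*Protocol article*

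**What the plan says.** Section 2.9 counts intervention costs, recruitment costs, costs of health care use, and "costs stemming from losses in productivity, in both paid work and volunteer jobs". For the components that vary most from parent to parent, the source is a questionnaire, abbreviated TiC-P: "The data on costs stemming from health care uptake and losses in productivity will be collected using the Trimbos/iMTA Questionnaire on Costs associated with Psychiatric". The numerator of the cost-effectiveness ratio is then defined: "The incremental costs will be calculated as the average cost difference between the conditions". Uncertainty is handled by resampling: "To manage stochastic uncertainty, 2500 non-parametric bootstraps will be used and the bootstrapped ICERs will be plotted on the ICER plane". Robustness is examined in one further way: "the CEA will be completed by performing one-way sensitivity analyses directed at uncertainties in major cost-drivers".

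Three other sections bear on the point.

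- Section 2.5 sets two measurement occasions, one at the start and one at three months: "All parents will receive a personal invitation by e-mail to complete two questionnaires online". It does not say at which of them the TiC-P is completed.
- Section 2.6: "Parents will be stratified by educational level", and also by implementation channel and daily cigarette consumption. No care-use or employment variable is among the strata.
- Section 2.10 gives a general rule: "In case of group differences at baseline, confounding variables will be included in subsequent analyses". It neither names nor excludes the cost analysis.

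**The concern.** A parent who is in treatment or on sick leave at baseline may well remain costly over the next three months. If so, baseline cost carries information about follow-up cost, and a comparison that ignores it is noisier than necessary. It also keeps whatever chance difference in baseline cost the randomisation happened to produce.

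Nothing else in the article clearly deals with this. The strata do not balance care use or work loss. One-way variation of cost drivers tests the inputs; it does not address costlier parents having landed in one arm. The bootstrap resamples the arms as realised, so its cloud shows the uncertainty but stays centred on the observed difference.

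The rule in section 2.10 might help, but its reach is unclear. At stake are the precision of the incremental cost and the location of the cost-effectiveness ratio in a trial whose economic result is meant for decision-makers.

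**Working it through.** **Inputs from the protocol article.** Sections 2.1 and 2.7: 158 parents in total, equal allocation (36 and 36 within each approach), anticipated drop-out 10%, planning rates 0.445 and 0.121, power 0.80, α 0.05. Section 2.9: 2500 bootstrap samples.

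**Inputs not in the article, assumed.** Correlation ρ between a parent's baseline and follow-up cost: 0.3 to 0.7. Standard deviation (SD) of cost: 500 to 3,000 euros, for illustration only.

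**Step 1. Reproduce the plan's sample size.** A two-sided comparison of 0.445 with 0.121 at α 0.05 and 80% power, with continuity correction, gives 36 per arm. That is 72 per approach and 144 for two approaches. Then 144 × 1.10 = 158.4, stated as 158. Per arm: 158 / 2 = 79 randomised, and 158 × 0.90 / 2 = 71.1, about 71 with follow-up. The plan's figures reproduce.

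**Step 2. Standard error (SE) of the simple cost difference**, in SD units: √(2/n).
- n = 79: √(2/79) = 0.159
- n = 71: √(2/71) = 0.168

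The same formula gives the chance SE of a difference in mean baseline cost. For 79 per arm, the 95% range is ±1.96 × 0.159 = ±0.31 SD.

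**Step 3. SE after regression on baseline cost:** √(2/n) × √(1 − ρ²).

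| ρ | √(1 − ρ²) | SE, n = 79 | SE, n = 71 | Reduction in SE |
|---|---|---|---|---|
| 0.3 | 0.954 | 0.152 | 0.160 | 4.6% |
| 0.5 | 0.866 | 0.138 | 0.145 | 13.4% |
| 0.7 | 0.714 | 0.114 | 0.120 | 28.6% |

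**Step 4. What a chance imbalance leaves in the simple difference.** If mean baseline cost differs by one SE, the unadjusted follow-up difference is expected to shift by ρ × √(2/n). For n = 71 this is 0.3 × 0.168 = 0.050 SD up to 0.7 × 0.168 = 0.117 SD.

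**Step 5. In euros, for illustration.** Shift = ρ × 0.1678 × SD.
- Low end (ρ = 0.3, SD 500): 25.2 euros per parent
- High end (ρ = 0.7, SD 3,000): 352.5 euros per parent

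Dividing by the planning effect, 0.445 − 0.121 = 0.324, gives about 78 to 1,088 euros per extra quitter. These amounts scale directly with the assumed SD.

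**Step 6. Read sections 2.9 and 2.10 together.** If the section 2.10 rule does not reach costs, the analysis is the simple difference of step 2. If it does, the cost estimator depends on whether an imbalance is noticed, so it is not fixed in advance, and the gain in step 3 is forgone whenever the arms look similar. Neither reading gives a prespecified adjusted estimate.

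The formulas take parents as independent, with a linear relation and equal variances. Section 2.6 randomises couples together, which is ignored here.

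**The case against.** The strongest reply is that this is a preference for efficiency, not the correction of an error. Under randomisation the simple difference in mean cost is unbiased. Chance imbalance is ordinary sampling variation, and the bootstrap, the plane and the acceptability curve exist to display it. The one-SE shift in step 4 is ρ times the SE of the unadjusted difference, so at the assumed correlations it lies inside the uncertainty that will be shown. All of this stands.

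It can also be said that section 2.9 does not use the word unadjusted, that an adjusted mean difference would fit its sentence, and that section 2.10 may already provide for imbalance. This stands in part. The sentence is most naturally read as a simple difference, but it does not rule out adjustment. The section 2.10 rule, even if it applies, acts only on observed imbalance.

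Four stronger readings are tempting, and the document supports none of them:
- A reader might infer that the plan expressly commits to a raw difference. It only names no adjustment.
- A reader might infer that the estimate is biased or the bootstrap wrong. Neither follows.
- A reader might infer that a few costly parents could carry the bootstrap cloud into another quadrant. That depends on the size of the mean incremental cost, which the article does not give.
- A reader might infer that baseline costs are collected and then ignored. The article does not say when the TiC-P is completed.

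The skewness of costs and their persistence within a parent are likewise expectations, not statements in the article.

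**Conclusion.** The point holds as an avoidable loss of precision and an unclear rule, not as a flaw that invalidates the economic evaluation. Section 2.9 names no baseline-cost adjustment, and section 2.10 leaves open whether costs fall under its conditional rule. With 79 parents per arm randomised and about 71 followed up, adjustment would shrink the SE of incremental cost by about 5% (ρ = 0.3) to 29% (ρ = 0.7). It would also remove the part of a chance baseline imbalance that carries over to follow-up, which is 0.050 to 0.117 SD for a one-SE imbalance.

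The percentages rest wholly on the assumed correlations, and the euro figures also on the assumed SD. At the lower end the gain is small. The change is still worth making, because it costs little and fixes the cost estimator before the data are seen.

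**What to change.** 1. State in section 2.5 or 2.9 that the TiC-P cost items are completed at both planned assessments, and add them to the baseline questionnaire if they are not there.
2. Define incremental cost in section 2.9 as the arm coefficient from a regression of follow-up cost on arm and baseline cost, used regardless of any observed imbalance.
3. In each of the 2500 bootstrap samples, refit this regression together with the effect estimate, so that cost and effect stay paired.
4. Report the unadjusted mean difference as a sensitivity analysis.
5. State in section 2.10 that its conditional rule does not govern the cost analysis.

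Cost: a few more minutes per parent at baseline if the items are not already collected, slightly more analysis work, and revised wording in sections 2.5, 2.9 and 2.10. The sample size is unaffected.

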
### 2.10. Statistical Analyses

Statistical analyses will be carried out to assess whether the randomization results in an equal baseline distribution of relevant participant characteristics across conditions. In case of group differences at baseline, confounding variables will be included in subsequent analyses. All analyses will be conducted in accordance with the intention-to-treat principle (i.e., all parents randomized to one of the two conditions will be included in the analyses examining the study hypotheses) as per the Consolidated Standards of Reporting Trials [53]. Moreover, a completers-only analyses will be conducted, i.e., only parents with outcome data on all assessments will be included in the analyses. To compare cessation rates across different groups, logistic regression analyses will be conducted. In addition, Mplus will be used to test for moderation and subsequently, multi-group testing with bootstrapping will be conducted to assess differences between recruitment approaches. Effect sizes and 95% confidence intervals (CI) will be reported to determine the magnitude and effect of the intervention.

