### 2.7. Sample Size

Based on the results of Schuck and colleagues (2014) [14], our power calculation (Stata 12.1, StataCorp., College Station, TX, USA) indicated that 72 parents per implementation approach (36 intervention and 36 control) is sufficient to detect 7-day prevalence abstinence at three months post-intervention with a large effect (*p*_1_ = 0.445, *p*_2_ = 0.121, Power = 0.80, α = 0.05). Because we want to examine differences in smoking cessation rates between the two implementation approaches, we have to double from 72 to 144 parents. Based on the drop-out rates at 3-month follow-up of Schuck et al., 2014 [14] (i.e., 10% in the control group and 3.9% in the intervention group), we will anticipate 10% drop-out. This means that we will aim to recruit a minimum of 158 participating parents in total.

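### Covariates enter the effectiveness analysis only when the arms differ at baseline, so the primary model is not fixed in advance and would almost never include the stratification factors

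*Protocol article*

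**What the plan says.** Section 2.10 of the protocol article opens with a check of balance: "Statistical analyses will be carried out to assess whether the randomization results in an equal baseline distribution of relevant participant characteristics across conditions". The action that follows is: "In case of group differences at baseline, confounding variables will be included in subsequent analyses". The section names no test, no threshold and no list of characteristics, and it does not define a confounding variable.

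The effectiveness model is given in one sentence: "To compare cessation rates across different groups, logistic regression analyses will be conducted". No covariate is attached to it. Recruitment approach appears only in the separate moderation and multi-group analysis.

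Section 2.6 sets three stratification factors. It begins "Parents will be stratified by educational level" (three levels). The second factor is the recruitment channel, with four levels. The third factor, with three levels, is "number of cigarettes smoked per day (i.e., less than 10; 10–20; 21 or more"). That makes 3 × 4 × 3 = 36 strata. The section mentions a computer-generated sequence but no blocking. No part of the article carries these factors into the analysis model.

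**The concern.** Under sound randomisation any baseline difference between arms is chance. A balance check therefore cannot reveal confounding in the usual sense; it selects covariates by the luck of the draw. Two consequences follow.

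1. The primary model is unknown until the data have been seen. Odds ratios are non-collapsible, so adding or omitting a prognostic covariate changes the quantity being estimated as well as its precision.
2. The rule works against the design. Stratification is meant to balance education, channel and cigarettes per day, so a rule triggered by imbalance leaves out the very factors used to allocate parents. If they are prognostic, the unadjusted model-based standard error is too large for the stratified design: the test is conservative and power is lost.

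At stake are the reproducibility of the primary estimate and some precision.

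**Working it through.** **1. The plan's own figure.** Section 2.7 gives rates 0.445 and 0.121, power 0.80, α 0.05 and 36 per arm per approach. The mean rate is 0.283 and the difference 0.324.

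n = [1.96·√(2·0.283·0.717) + 0.8416·√(0.445·0.555 + 0.121·0.879)]² / 0.324² = (1.2486 + 0.5003)² / 0.1050 ≈ 29.1, that is 30 per arm.

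With the continuity correction: (29.1/4)·[1 + √(1 + 4/(29.1·0.324))]² ≈ 35.0, rounded up to 36. Then 2 × 36 = 72, doubled to 144, and 144 × 1.10 = 158.4, the stated 158. The figure reproduces, and covariate adjustment does not alter it.

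The planned odds ratio is (0.445/0.555)/(0.121/0.879) ≈ 5.8. Expected quitters are 72 × 0.445 + 72 × 0.121 = 32.0 + 8.7 ≈ 41.

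**2. Would the rule ever admit a stratifier?** Assumptions: N = 158, permuted blocks of 4 within the 36 strata, assumed factor distributions, and a chi-square test at 5% for each factor (3,000 trials).

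| Allocation | Education flagged | Channel flagged | Cigarettes flagged | Any |
|---|---|---|---|---|
| Simple randomisation | 5.2% | 5.2% | 5.4% | 15% |
| Stratified, blocks of 4 | 0% | 0% | 0% | 0% |

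In a separate check at N = 158 (1,500 trials per scenario), blocks of 2, 4 and 6 gave 0%, 0% and about 0.1%. Within one approach (n = 72, blocks of 4) the figure was under 1%.

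**3. How often would the rule change the model through other covariates?** With six independent baseline variables (number assumed) tested at 5%, the chance of at least one flag is 1 − 0.95⁶ = 26.5%. Simulation gave 25–28%.

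**4. Power without and with the stratifiers.** Prognostic strength is assumed throughout and given as log-odds per level. Because the rule flagged (almost) no stratifier, its power equals that of the unadjusted model.

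| Setting | Without | With |
|---|---|---|
| OR e^0.9 ≈ 2.5, N = 158, factors not prognostic | 70.8% | 72.4% |
| Same, moderate (education and cigarettes 0.6, channel 0.36) | 66.6% | 71.2% |
| Same, strong (1.0, 1.0, 0.6) | 56.8% | 67.0% |
| OR 3, N = 144, effects 0.5–0.8, two scenarios | 76.0%; 74.8% | 78.4%; 78.9% |
| OR 3, N = 158, about 0.6 | 79–81% | 82–84% |
| OR 3, N = 158, about 0.9 | 75–77% | 81–83% |
| Planned 0.445 v 0.121, pooled, N = 144 | 99.5–99.8% | 99.7–99.9% |
| Planned rates, one approach, n = 72 | 89–90% | 91–93% |

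A further run put the gain at roughly 0–5 points at an odds ratio of 3 and about 1–3 points within one approach. The strongest settings go beyond that: about 6 points at an odds ratio of 3 and 10 points at 2.5. The latter assumes odds of quitting that differ by e² ≈ 7.4 between the lowest and highest education level, so it marks an outer edge.

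**5. Type I error (nominal 5%, about 1,200 trials).** Under the rule v with the factors always in: 3.8% v 4.1% (not prognostic), 4.7% v 5.7% (moderate), 3.0% v 5.0% (strong). The simulation standard error is √(0.05·0.95/1200) ≈ 0.63 points. Only the strong setting departs clearly from nominal: (5.0 − 3.0)/0.63 ≈ 3.2 standard errors, in the conservative direction.

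**6. Shift in the estimate.** With a conditional odds ratio of 3, the median estimate was about 2.6–2.8 unadjusted and 3.1–3.2 adjusted.

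**The case against.** **The wording is loose.** No significance test or 5% threshold is stated, and a confounding variable should also relate to outcome, so the rule may not select purely on imbalance. Both points are fair, and the 5% test above is an assumption. Yet the only stated trigger for adjustment is still a difference between arms.

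**A condensed article may leave model terms to an analysis plan.** True of a silence. Here the article states a rule, and a plan that fixed covariates regardless of balance would depart from it. It remains fair that the exclusion of the stratifiers is a consequence of the rule and not a sentence in the text.

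**Balance is assumed.** No block size is given, 158/36 ≈ 4.4 parents per stratum is thin, and couples are allocated by household, which was not modelled. Balance could be weaker than simulated. If allocation behaved like simple randomisation, some stratifier would enter by chance in about 15% of trials, which is no better as a rule.

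**Prognostic value is not documented.** A reader might infer that the factors were chosen because they predict quitting. Section 2.6 gives no reason, and channel is also the unit of the implementation comparison. This objection stands, and it makes every power gain conditional.

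**At the planned effect the pooled gain is nil.** This stands: at most 0.2 points.

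**Many-term models can fail.** This also stands. In one run with all four channels in the model and 12% quitting in both arms, 12–22% of pooled fits (N = 144) and 39–57% of single-approach fits (n = 72) did not converge or gave extreme coefficients. Another run found about 4–17% at n = 72. At the planned rates pooled failures were rare (0.1%). The remedy must therefore stay small and handle sparse data.

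**Conclusion.** The concern holds as a matter of analysis choice. The article fixes a data-dependent covariate rule, leaves the primary model and its odds ratio to chance imbalance, and in practice keeps out the three factors used for allocation. That the model is not fixed in advance holds for any randomisation method. The near-certain omission of the stratifiers assumes blocking or something similar.

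The cost in power is modest and depends on assumptions: roughly 0–5 points at an assumed odds ratio of 3, negligible for the pooled comparison at the planned rates, and about 1–3 points within one approach.

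A reader might infer that the rule inflates false positives or leaves the pooled comparison underpowered. Neither is supported. Type I error showed no inflation under the rule, and pooled power at the planned rates exceeds 99% either way. The change is worth making because it is nearly free, not because the trial's conclusion is in danger.

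**What to change.** In section 2.10, replace the conditional-adjustment rule with a pre-specified primary model: logistic regression of 7-day abstinence on condition, with education (three levels), cigarettes per day (three levels) and channel collapsed to approach (two levels) as main effects, whatever the baseline comparison shows. Baseline characteristics may still be described by arm, but not used to select covariates.

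State in advance how sparse data will be handled, for example by pooling sparse levels in a fixed order or by a penalised (Firth) fit. This applies above all to single-approach analyses, where the approach term drops out.

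The cost is small. The factors are already recorded for randomisation and the target of 158 does not change. The model has 1 + 2 + 2 + 1 = 6 terms for about 41 expected quitters, or 41/6 ≈ 7 per term; the 36 strata could not be fitted. Collapsing channel to approach gives up some of the stratification information in exchange for a more stable fit. The report should say that the resulting odds ratio is conditional on these factors.

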The existing research suggests that most parents want to quit smoking and even tried to quit smoking [10]. In addition, most parents would accept smoking cessation support, such as telephone counseling [11]. A review consisting of 77 (quasi) randomized controlled trials (RCT) on telephone counseling confirmed that telephone counseling is effective in increasing smoking cessation rates [12]. Moreover, Hollis et al., 2007 [13] found that telephone counseling is cost-effective (i.e., the degree to which something is effective in relation to its costs). Recently, a tailored telephone counseling program for smoking parents was tested in The Netherlands [14]. Parents who smoke (*N* = 512) were recruited in an RCT and assigned to the intervention condition (i.e., tailored telephone counseling and supplementary materials) or the control condition (i.e., a standard self-help brochure). Parents who received telephone counseling were more likely to report 7-day point prevalence abstinence at three months post-intervention (44.5% versus 12.1%; OR = 6.89, 95% CI = 4.18–11.36) and to use nicotine replacement therapy (48.4% versus 20.9%) compared to parents who received a standard self-help brochure. Among parents who did not quit smoking, those who received telephone counseling were more likely to make a quit attempt (85.2% versus 68.1%) and to implement a complete home smoking ban (39.5% versus 26.1%) compared to parents who received the self-help brochure. Altogether, this study provided evidence that telephone counseling tailored to smoking parents is effective in helping parents quit smoking and developing parenting practices that protect their offspring from ETS exposure [14].

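### The bootstrapped comparison between recruitment approaches rests on about four expected control quitters per approach; on the odds-ratio scale with percentile limits, about half of trials would have an unbounded interval

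*Protocol article*

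**What the plan says.** Section 2.10 of the protocol article compares cessation rates by logistic regression. For differences between recruitment approaches it adds that "Mplus will be used to test for moderation and subsequently, multi-group testing with bootstrapping will be conducted". It promises effect sizes with 95% confidence intervals, an intention-to-treat analysis of all randomised parents, and a completers-only analysis. For the bootstrap step it gives no effect scale, interval type, number of resamples or handling of resamples with an empty cell.

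Section 2.7 fixes the cell size as "72 parents per implementation approach (36 intervention and 36 control". It takes its rates from the earlier efficacy trial, reported in the Introduction as "44.5% versus 12.1%; OR = 6.89, 95% CI = 4.18–11.36". Because differences between approaches are of interest, the authors write that "we have to double from 72 to 144 parents". They then say "we will anticipate 10% drop-out" and "we will aim to recruit a minimum of 158 participating parents in total".

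**The concern.** A bootstrap of an odds ratio fails when resamples often contain no event in one arm. The arm coefficient then diverges (quasi-complete separation) and that resample's odds ratio is infinite. Once such resamples exceed 2.5% of the total, a 95% percentile interval has no finite upper limit. The planned control cells are small enough, and the planned control rate low enough, for this to be common.

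What is at stake is the comparison between approaches, for which the sample was doubled. Its interval could be unbounded, or finite only because the software capped or discarded the failed resamples without saying so.

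**Working it through.** **Inputs.** Control rate 0.121, intervention rate 0.445, power 0.80, α 0.05, 36 per arm per approach, 144 before drop-out and 158 recruited (section 2.7; rates also in the Introduction). Assumptions not in the protocol: two-sided α, an equal split between approaches, and a percentile bootstrap of the odds ratio with empty-cell resamples kept.

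**The plan's own figure.** The two-proportion formula gives 30 per arm without continuity correction and 36 with it. So 2 × 36 = 72 per approach and 2 × 72 = 144 in total; 144 × 1.1 = 158.4. The stated sizes reproduce.

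**Expected control quitters per approach.** 36 × 0.121 = 4.36. With 158 split equally, 158/4 = 39.5 per cell: 39 × 0.121 = 4.72 and 40 × 0.121 = 4.84.

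**When the upper limit is lost.** With k quitters among 36 controls, a resample has none with probability (1 − k/36)^36:
- k = 2: 0.128
- k = 3: 0.044
- k = 4: 0.014

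The 0.025 mark is crossed at k ≤ 3. The threshold is the same at 39 and 40 per cell, and also when whole approach groups are resampled instead of arms.

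**How often this happens.** P = P(K ≤ 3) for a binomial with rate 0.121; for at least one of two approaches, 1 − (1 − P)².

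| Controls per approach | P, one approach | At least one approach |
|---|---|---|
| 36 | 0.352 | 1 − 0.648² = 58.0% |
| 39 | 0.289 | 49.5% |
| 40 | 0.271 | 46.8% |

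Simulation with 2500 resamples (the number the protocol gives only for its economic evaluation) returned 58%, 50% and 47%.

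**Sensitivity to the control rate** (at least one approach; 40 per cell to 36 per cell):
- 10%: 67% to 76%
- 12.1%: 47% to 58%
- 14%: 31% to 42%
- 20%: 6% to 10%

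**Sensitivity to the split between approaches.** A 40:60 split gives 54% (158 parents) or 63% (144 parents).

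**Other bootstrap intervals on the odds-ratio scale.** By simulation, bias-corrected limits are unbounded in 51%, 45% and 43% of trials at 36, 39 and 40 per cell. An interval built on the bootstrap standard error fails in 98–99%, because one infinite resample is enough.

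**Dropping empty resamples.** With 16/36 intervention quitters:
- Three control quitters: the odds ratio is (16/20)/(3/33) = 8.8. Discarding empty resamples gives an upper limit of about 39; the Wald limit is 34.
- Two control quitters: the odds ratio is (16/20)/(2/34) = 13.6. The clipped upper limit is about 44; the Wald limit is 65.

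The point estimate comes from the full sample and does not change.

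**Without the bootstrap.** An ordinary profile-likelihood or exact interval is unbounded only if an observed control cell is empty. For at least one approach: 1 − (1 − 0.879^36)² = 1.9% at 36 per cell, 1.3% at 39 and 1.1% at 40.

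**Precision that remains.** The variance of the log odds ratio in one approach is 1/16.02 + 1/19.98 + 1/4.356 + 1/31.64 = 0.374. For the difference between two approaches it is 0.747, so the standard error is 0.864. exp(1.96 × 0.864) ≈ 5.4, so a Wald-type interval for the ratio of odds ratios extends about 5.4-fold each way.

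**The case against.** The strongest reply is that the protocol does not fix the details on which the figure depends. It names no scale or interval type for this step. The multi-group step could be a test of equal parameters with no approach-specific limit, and the sentence on confidence intervals does not say they come from the bootstrap. A condensed article may leave such details to an analysis plan. This stands as a limit on the claim: the percentages are conditional. It does not remove the point, because logistic regression is the stated model for cessation rates and points to the odds-ratio scale. On that scale the other bootstrap intervals fail too, and dropping or capping resamples only changes how the failure shows.

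Three stronger readings are tempting, and the documents do not support them.
- A reader might infer that the stated method by itself makes the interval fail in most trials. Under intention to treat with all 158 parents the figure is just under half. A higher control rate than 12.1% is as open as a lower one, since recruitment routes differ from the efficacy trial's and an intention to quit is required.
- A reader might infer that discarding failed resamples biases the odds ratio downwards. It alters only the upper tail of the interval, and at three control quitters the result (39 against 34) is not unusable.
- A reader might infer that the fix rescues the comparison. The interaction estimate stays very imprecise because of the sample size, and a moderation test is already planned before the bootstrap step.

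**Conclusion.** The point holds in conditional form. At the planned cell size and control rate, a percentile bootstrap of the odds ratio that keeps empty-cell resamples has no finite upper 95% limit for at least one approach in about 58% of trials at 36 per cell, and in 47–50% with all 158 analysed and split equally. The problem nearly disappears if the control rate is about 20%.

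It concerns only the comparison between approaches; the pooled primary comparison of counselling with brochure is unaffected. The bootstrap is the main cause of the unbounded limits, since a likelihood-based interval has the problem in only 1–2% of trials. It is worth correcting because a better method is readily available, but the correction does not make this comparison precise.

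**What to change.** Replace the bootstrapped multi-group step in section 2.10 with one logistic model containing arm, approach and arm-by-approach, fitted with Firth penalisation and with profile-likelihood intervals. Alternatively, keep the bootstrap but apply it to the difference between approaches in risk differences, which is finite in every resample. Report the approach-specific effects from the analysis chosen.

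The cost is a change of analysis wording and the use of standard software, with no extra parents or data. The downside is that Firth estimates are slightly shrunk.
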